Box 1Study endpointsPrimary endpointSustained steroid/exclusive enteral nutrition (EEN)-free remission at month 12, where sustained remission is defined as weighted Paediatric Crohn’s Disease Activity Index (wPCDAI) ≤12.5 and C reactive protein (CRP) ≤1.5 times the upper limit without a relapse or need for EEN/steroids since week 12.Secondary endpointsComparing the following within (1) the two treatment arms per risk group; (2) methotrexate treatment between high and low-risk groups and (3) tOP-down adalimumab (high-risk group) versus step-pp adalimumab (ancillary study):Rate of clinical remission at month 12 (physician global assessment, wPCDAI, PCDAI).Relapse free remission with normal CRP at month 12.Relapse-free remission with normal CRP and faecal calprotectin <300 at month 12.Remission at week 12 (measured by wPCDAI≤12.5 and normal CRP and being off steroids/EEN).Time to first relapse after week 12.Predictive value of faecal calprotectin values at visits 1, 2, 4 and 6 (respectively at month 0, 2, 6 and 12).Drop-out rates.Adverse drug event rate including pharmacogenomics for toxicity and response to therapy.Height velocity and z-score at baseline and 52 weeks.Quality of life as measured by the IMPACT 3 questionnaire completed at each study visit.Health economic evaluation at all visits (forms EQ-5D-Y proxy 1, EQ-5D-Y and EQ-5D-5L, Productivity and Activity Impairment Questionnaire (WPAI):Crohn’s disease Caregiver, School Attendance start of the research and follow-up visits).

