### Secondary analyses

X^2^ tests or Fisher’s exact tests will be used to compare rates of remission, steroid intake, drop-out and SAEs between the two arms of each risk group and between the low and high-risk MTX groups. Logistic regression analyses may be performed to adjust for any imbalances in baseline covariates. To compare time to disease flare between the arms of each risk group and between high and low-risk MTX groups, a Kaplan-Meier survival estimate will be used and the log-rank test of equality over strata. A Cox proportional hazard model will be constructed to obtain a HR after validation of the proportionality assumption and adjusting for possible confounding variables (including age and disease duration). Student’s t tests or Wilcoxon rank sum tests will be used to compare growth, steroid dose, adverse events, changes in quality of life and patient reported outcomes between the two arms of each risk group and between the high and low-risk MTX groups. The predictive value of faecal calprotectin levels, CRP, serum tests or other clinical predictors for response (including genomic and serological markers) will be assessed for each arm of the study using sensitivity, specificity, negative and positive predictive values or area under the receiver operating characteristic curve. Multivariate logistic regression analyses will then be performed.

Analyses will be performed using the R software (http://cran.r-project.org). All comparisons will be made using a two-sided significance level of 0.05.

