#### Sample size considerations

Estimated remission rates are based on recent analysis from the RISK study,^18^ indicating an advantage of early anti-TNF introduction over immunomodulator therapy. For the low-risk group, it was hypothesised that 48% of children will be in remission at 12 months for the AZA/6MP arm versus 70% for the MTX arm. On the basis of this data with an alpha risk of 5% and a power of 80% a sample requirement of 88 patients per arm was calculated assuming a 10% lost to follow-up. For the high-risk group, it was hypothesised that 40% of children will be in remission at 12 months for the MTX arm versus 65% for the ADA arm. To detect this difference with an alpha risk of 5% and a power of 80%, a sample size of 68 participants is necessary, again assuming a 10% lost to follow-up. In total 312 participants will be included in the study (176 low-risk group; 136 high-risk group).

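### Growth and quality-of-life comparisons leave baseline-adjusted precision unused, and the adverse event rate is tested without a stated time window or denominator

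*Protocol article*

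**What the plan says.** Secondary analyses in the protocol article assigns several outcomes to two-group tests: "t tests or Wilcoxon rank sum tests will be used to compare growth, steroid dose, adverse events, changes in quality of life", together with patient-reported outcomes. They apply to the two arms in each risk group and to high- versus low-risk methotrexate (MTX) patients. The section ends: "All comparisons will be made using a two-sided significance level of 0.05".

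Box 1 lists the endpoints as "Height velocity and z-score at baseline and 52 weeks", IMPACT 3 at every study visit, and "Adverse drug event rate including pharmacogenomics for toxicity and response to therapy".

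The only adjusted models in the section are logistic regression (optional, for baseline imbalance, and again for predictors of response) and a Cox model for time to flare. Serious adverse events are compared as proportions by chi-square or Fisher tests. Randomisation is stratified by induction therapy (steroids or enteral nutrition).

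Four places bear on time at risk:
- Box 4: failure on MTX or thiopurine leads to an offer of the step-up adalimumab (ADA) study or exit; failure on ADA leads to more frequent dosing.
- Ancillary study: the initial drug is stopped on entry.
- Treatment discontinuation: early stoppers get one further visit, either 12 months after treatment start or on entry to the ancillary study.
- Box 5: treatment failure is a ground for ending study treatment, with no exception for ADA.

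**The concern.** For continuous outcomes, a follow-up value is usually predicted in part by its baseline. A t or Wilcoxon test on changes uses the baseline inefficiently, and one on final values does not use it at all. The cost is power in a trial sized for its primary endpoint only.

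The MTX high- versus low-risk contrast is a different matter. It is not randomised, and Table 1 makes severe growth impairment one of the criteria for high risk. Height z-score therefore differs between these groups at baseline by design, and an unadjusted growth test partly reports how patients were classified.

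For adverse events, a rate needs observed time. The failure rules make it plausible that time on the randomised drug differs by arm. If counting stops with the drug or at the switch, the arm with more early stops accrues fewer events merely because it is watched for less time. That comparison informs the choice of drug in children.

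**Working it through.** **Patients available.** The plan's sizes come first, because they set the evaluable numbers. Inputs: "48% of children will be in remission at 12 months for the AZA/6MP arm versus 70% for the MTX arm"; "40% of children will be in remission at 12 months for the MTX arm versus 65% for the ADA arm"; 5% two-sided alpha, 80% power, 10% loss. The pooled-variance formula for two proportions, without continuity correction, gives 78 per arm (low risk) and 62 (high risk). Then 78/0.9 = 87 against 88 stated, and 62/0.9 = 69 against 68 stated (read as per arm, since the group total is 136). The plan's figures reproduce within one patient. Evaluable per arm after 10% loss: 88 × 0.9 ≈ 79 and 68 × 0.9 ≈ 61.

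**Precision for growth and quality of life.** Take equal variance at baseline and 12 months and correlation r; r is an assumption, as the article gives none. Relative variances of the arm contrast are 1 for the 12-month value, 2(1−r) for the change and 1−r² for ANCOVA. Hence ANCOVA/change = (1−r²)/[2(1−r)] = (1+r)/2.

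| r | ANCOVA/change | ANCOVA/12-month value |
|---|---|---|
| 0.3 | 0.65 | 0.91 |
| 0.5 | 0.75 | 0.75 |
| 0.7 | 0.85 | 0.51 |
| 0.8 | 0.90 | 0.36 |
| 0.9 | 0.95 | 0.19 |

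Power for an assumed difference of 0.4 SD, change score then ANCOVA:
- Low risk (79 per arm): 71% to 83% at r = 0.5; 90% to 94% at r = 0.7.
- High risk (61 per arm): 60% to 72% at r = 0.5; 81% to 87% at r = 0.7.

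**Adverse events, if counted only on randomised drug.** Assumptions: the planned remission proportion p completes 12 months on drug, everyone else stops at month t, and the true event rate is the same in both arms. Mean exposure = 12p + (1−p)t.

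High risk, MTX (p = 0.40) against ADA (p = 0.65):
- t = 3: 4.8 + 1.8 = 6.6 against 7.8 + 1.05 = 8.85; ratio 0.75.
- t = 6: 4.8 + 3.6 = 8.4 against 7.8 + 2.1 = 9.9; ratio 0.85.
- t = 9: 4.8 + 5.4 = 10.2 against 7.8 + 3.15 = 10.95; ratio 0.93.

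So MTX would show 25%, 15% or 7% fewer events. At an assumed 2 events per patient-year with Poisson counts, a normal-approximation test of mean counts would reject in about 34%, 18% or 8% of trials, against a nominal 5%. In the low-risk group (thiopurine p = 0.48, MTX p = 0.70) the thiopurine count would be 21%, 13% or 6% lower.

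If instead every ADA failure stayed on drug for 12 months, the MTX/ADA ratios would be 6.6/12 = 0.55, 8.4/12 = 0.70 and 10.2/12 = 0.85. Box 4 permits that reading; Box 5 points the other way.

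**The case against.** A reader might infer that baseline values are ignored altogether. The article does not support this. Quality of life is compared as a change, height velocity is a change by construction, and the descriptive statistics foresee paired differences where applicable. The large gains in the right-hand column of the table apply only if raw 12-month height z-score is compared, which the article does not say. The unadjusted tests are valid between randomised arms, so the issue there is efficiency. Covariates for secondary outcomes are also often left to an analysis plan. That last argument carries limited weight here, because the article does name the tests.

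A reader might also infer that the safety comparison is biased as planned. That is not established:
- No counting window is given. With events counted by randomised arm over an equal 12 months, unequal observation disappears. Serious events are in fact followed from consent until resolution or 30 days after the end of the study or the final visit, and step-up patients keep attending visits.
- The article does not say that raw counts are tested. A per-patient rate could be fed into either named test.
- Non-remission is not the same as stopping the drug. A mildly raised activity score at month 12 alone misses the primary endpoint without meeting the relapse rule, which requires two consecutive visits.
- Toxicity itself can end treatment, so an offset for time on drug is not a neutral correction.

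All four points stand and make the safety limb conditional. They do not remove it. Under the equal-follow-up reading, events on ADA after a switch would count against MTX or thiopurine, which is hard to call a drug event rate for those drugs. Either way the window and denominator need stating.

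**Conclusion.** The point holds in three parts of unequal weight.

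1. **Randomised comparisons of growth and quality of life:** a loss of precision, not bias. The loss against ANCOVA is modest for change scores (10–25% of variance at r = 0.5–0.8, 5% at r = 0.9), and larger only if raw final height z-score is tested. The correlations are assumed.
2. **High- versus low-risk MTX:** an unadjusted growth test is confounded by the definition of the groups. Baseline adjustment would reduce this without fully curing it.
3. **Adverse events:** a rate is named, but its window and denominator are not. The 7–25% shortfall on MTX in the high-risk group is illustrative. It rests on counting only on randomised drug, on non-remission standing in for stopping, and on the assumed stopping times.

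These are secondary analyses and the primary endpoint is untouched. The change is still worth making before analysis.

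**What to change.** - Analyse 12-month height z-score and IMPACT 3 by ANCOVA with the baseline value and induction stratum as covariates. A repeated-measures model is an alternative for IMPACT 3, which is collected at each visit.
- For high- versus low-risk MTX, present the baseline-adjusted growth estimate as non-randomised, with residual confounding acknowledged.
- State the adverse event counting window: on randomised drug, until entry to the ancillary study, or the full 12 months by randomised arm. Say how events after a switch to ADA are attributed.
- Compare event rates by Poisson or negative binomial regression with the log of observation time in that window as offset. Note that time on drug may itself depend on toxicity.
- Keep chi-square or Fisher tests for the proportion with a serious adverse event.
- Reconcile Box 4 and Box 5 on what follows failure on ADA, since this determines exposure in that arm.

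The cost is analysis wording. Baseline values, visit-level IMPACT 3, medication review and adverse event review are already collected. The rate model also needs event and drug-stop dates, which I assume the case report form records.

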##### Induction therapy

All enrolled patients receive either corticosteroids or EEN as induction as determined by the clinical team and the patient/caregiver. For EEN any balanced formula (polymeric or elemental) administered orally or via nasogastric tube is permitted and should be prescribed for 6–8 weeks. Tapering of steroids is at the discretion of the prescribing clinician. Adaptation of induction therapy (eg, dose increase of steroids or return to EEN) or crossover from one induction therapy to the other is permitted in order to achieve remission, however, patients must have discontinued their induction therapy by week 12. If induction therapy is not discontinued by week 12, the patient is considered a treatment failure, with the protocol for this detailed below.

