#### Inclusion visit and risk group allocation (week 5±3 weeks; visit 1)

In order to incorporate response to initial induction therapy within the risk stratification criteria, inclusion and risk group allocation is performed at week 5±3 weeks of induction therapy. Data from the screening visit are reviewed with ineligible patients excluded and patients are then stratified into the high or low risk group (table 1) based on the European Crohn’s and Colitis Organisation/European Society for Paediatric Gastroenterology, Hepatology and Nutrition consensus guidelines.^1^ Patients with perianal fistulising disease at diagnosis are auto allocated to the high-risk group regardless of other factors at inclusion visit. All other patients are allocated to the low-risk group. Patients with low thiopurine methyltransferase (TPMT) activity or homozygous mutations are excluded should they be categorised as low risk.

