### Randomisation and treatment allocation

Randomisation is undertaken following allocation to high or low-risk group at week 5±3 weeks. This process uses an integrated module within the electronic case report form (CRF) system. Within both the high and low-risk groups patients are 1:1 randomised to MTX vs ADA or AZA/6MP, respectively, in blocks of four stratified by EEN or steroid induction therapy. Code for randomisation is prepared and held by the central coordinating site and site coordinators are then informed of the results. Immunomodulator or biological therapy should be commenced within 2 weeks of randomisation as per the protocol outlined in table 2.

**Table 2 T2:** Medication protocol for low and high-risk patients following randomisation

	Therapy	Route	Dose	Notes
Low risk protocol	Methotrexate	SC	15 mg/m^2^ body surface area weekly (max dose 25 mg).	Ondansetron 4–8 mg orally 1-hour preinjection and folic acid 15 mg (5 mg in patients <20 kg) 3 days postinjection are recommended for all patients.

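### Steroid dose is compared by tests that ignore the induction stratum used in randomisation; if induction steroid is counted, a real difference could easily be missed

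*Protocol article*

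**What the plan says.** All references are to the protocol article.

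- **Secondary analyses, dose.** Student's t or "Wilcoxon rank sum tests will be used to compare growth, steroid dose, adverse events" and other outcomes, between the two arms of each risk group. No stratification factor is named.
- **Secondary analyses, intake.** Chi-square or Fisher's "exact tests will be used to compare rates of remission, steroid intake, drop-out and SAEs between the two arms of each risk group". Again no stratification is named. The same tests serve the low-risk versus high-risk methotrexate comparison, which is not randomised and is not the subject of this point.
- **Secondary analyses, adjustment.** "Logistic regression analyses may be performed to adjust for any imbalances in baseline covariates". This is optional and does not name induction type.
- **Randomisation and treatment allocation.** Allocation is 1:1 within risk group, "in blocks of four stratified by EEN or steroid induction therapy".
- **Induction therapy.** "All enrolled patients receive either corticosteroids or EEN as induction as determined by the clinical team and the patient/caregiver". Switching between the two is allowed, the steroid taper is left to the clinician, and induction must end by week 12.
- **Inclusion visit.** "inclusion and risk group allocation is performed at week 5±3 weeks of induction therapy", and randomisation follows. Induction has therefore normally run for 2 to 8 weeks by then.
- **Box 1.** Neither steroid dose nor steroid intake appears in the endpoint list. The article gives no time window for either.

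**The concern.** Induction type is the strongest single determinant of induction steroid exposure. A child on exclusive enteral nutrition (EEN) who does not switch has an induction steroid dose of zero, whichever maintenance drug is allocated. The design uses this factor as a randomisation stratum, so the arms are nearly balanced on it. The named tests then leave it out, so the large gap between EEN and steroid children goes into the error term although it cannot contribute to the arm difference. The result is a test whose true error rate is far below 5% and whose power falls accordingly.

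The optional logistic regression does not repair this. It does not fit a continuous dose, and it is triggered by imbalance, which the blocks largely prevent.

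At stake is the reading of a null result. In a trial whose primary endpoint is remission free of steroids and EEN, a finding of no difference in steroid dose could be taken as evidence when the test had little chance of showing one.

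**Working it through.** **The plan's own figures.** No figure is given for the steroid comparisons, so the sample size is checked only to fix the number of evaluable children.

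n per arm = [1.96·√(2·p̄·q̄) + 0.8416·√(p₁q₁ + p₂q₂)]² / (p₁ − p₂)²

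- Low risk, 0.48 v 0.70: (1.363 + 0.571)² / 0.0484 = 77.3, so 78; 78/0.9 gives 87 (stated 88).
- High risk, 0.40 v 0.65: (1.384 + 0.575)² / 0.0625 = 61.4, so 62; 62/0.9 gives 69 (stated 68 per arm).

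These agree to within one child. After 10% loss, about 79 (88 × 0.9) and 61 (68 × 0.9) per arm are evaluable.

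**Assumptions, not in the document.** Steroid share s; coefficient of variation of dose among steroid children cv = 0.5; dose 30% lower in one arm. Crossover is 0 unless stated.

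**Information kept by the unstratified t-test.** Take a mean dose of 1 among steroid children and 0 among EEN children. The variance over the whole arm is s·cv² + s(1 − s), of which only s·cv² lies within the stratum. The ratio is cv²/(cv² + 1 − s):

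| s | Ratio |
|---|---|
| 0.3 | 0.25/0.95 = 0.26 |
| 0.5 | 0.25/0.75 = 0.33 |
| 0.7 | 0.25/0.55 = 0.45 |

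**The same for Wilcoxon ranks.** The tied zeros sit at the bottom. The ratio is s³/[1 − (1 − s)³]; at s = 0.5 it is 0.125/0.875 = 1/7.

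**Hand check of power, s = 0.5, 61 per arm.** Power of 79% within the steroid stratum means an expected z of 1.96 + 0.81 = 2.77. With the strata balanced, the unstratified tests reject only when the within-stratum z exceeds 1.96·√3 = 3.39 (t) or 1.96·√7 = 5.19 (Wilcoxon). The chances are about P(Z > 0.63) = 26% and P(Z > 2.42) = 0.8%. Simulation agrees:

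| Setting | t | Wilcoxon | Steroid stratum alone |
|---|---|---|---|
| 61 per arm, s = 0.5, no crossover | 22% | <1% | 79% |
| 79 per arm, s = 0.5, no crossover | 37% | 1% | 89% |
| 61 per arm, s = 0.5, 20% crossover | 42% | 21% | 78% |
| 79 per arm, s = 0.5, 20% crossover | 59% | 33% | 89% |
| 79 per arm, s = 0.7, no crossover | 78% | 67% | 96% |

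**All children kept, stratified test.** This uses a second model: lognormal dose with log-SD 0.5, 25% lower dose, 79 per arm. It compares the van Elteren test, which is Wilcoxon stratified by induction type, with the unstratified Wilcoxon.

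| EEN share | Crossover | Van Elteren | Unstratified |
|---|---|---|---|
| 30% | 0 | 82% | 29% |
| 50% | 0 | 69% | 0.1% |
| 70% | 0 | 47% | 0% |
| 30% | 20% | 77% | 52% |
| 50% | 20% | 54% | 14% |
| 70% | 20% | 29% | 4% |

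With no true difference and 50% EEN, the unstratified test rejects in 0 to 0.6% of trials and the stratified test in about 5%.

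**Yes/no intake.** With an assumed odds ratio of 0.4, Mantel-Haenszel by induction type gains about 4 to 12 points. At 79 per arm, power goes from 70% to 74% (30% EEN; control intake 20% in EEN and 60% in steroid children) and from 41% to 52% (50% EEN; 2% and 50%).

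**Window.** In the second model at 79 per arm, adding a pre-randomisation dose equal on average to the control arm's later dose cuts power from 94% to 63% with no EEN children, and from 82% to 44% for the stratified test at 30% EEN. If instead only steroid after week 12 is counted, with an assumed 40% v 20% later use equal in both strata, the stratified and unstratified tests agree within 0.3 points: 66 to 68% at 61 per arm and 77 to 78% at 79.

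**The case against.** The strongest case on the other side has five parts.

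1. **EEN children are not barred from steroids.** A reader might infer that this stratum takes none by design. The Induction therapy section does not support that: switching is allowed, and steroids may also be given later for relapse. This stands. Crossover reduces the loss but does not remove it.
2. **The article does not say which steroid is counted.** A reader might infer that pre-randomisation dose is included. No window is stated, and the full protocol or analysis plan may give one, so the missing window is not itself the fault. If only steroid after week 12 counts, as in the primary endpoint, the loss all but disappears. This stands and makes the point conditional.
3. **The steroid share is unknown.** At 70% steroids the unstratified t-test still reaches 78% with 79 per arm. It would be wrong to say that a real effect is bound to be missed, or that a null result is close to guaranteed.
4. **Intake is little affected.** This stands; the point rests on dose.
5. **Steroid dose is not a listed endpoint, and the error is conservative.** Both are true, and they limit the severity.

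None of this defends leaving the stratum out. When it does not matter, including it costs practically nothing; when it does, the gain is large.

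**Conclusion.** The point holds as a minor one. The choice of unstratified tests for steroid dose is stated in the article, and it sits badly with randomisation stratified by induction type. If induction steroid is counted and a sizeable share of children use EEN, the test is over-conservative and a real difference could easily be missed: about 22% (t) or under 1% (Wilcoxon) against 79% at 61 per arm, or 42% and 21% against 78% with 20% crossover. These figures rest on an assumed steroid share of one half, a dose coefficient of variation of 50% and a 30% reduction, none of which the article gives. No false positive arises, and the primary endpoint and the sample size are unaffected.

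**What to change.** In Secondary analyses:

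- Compare steroid dose over all children with induction type as a stratum, by the van Elteren test or a linear model with induction type as a factor. Name one in advance.
- Compare steroid intake by Mantel-Haenszel stratified by induction type.
- Count dose from randomisation onward, including steroid that is continued and not only steroid newly started, so that failure to wean is captured.

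Do not restrict the comparison to steroid-induced children. That would discard steroid given to EEN children who switch or relapse. Under the after-week-12 assumptions above, it would cut power to 51%, 38% and 24% at 30%, 50% and 70% EEN (61 per arm).

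The cost is a few words of analysis text. The stratum is already recorded for randomisation. One thing to confirm is that the case report form captures steroid dose with dates: Box 3 mentions a review of medications but not start and stop dates.
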